### Statistical analyses

Because the included CRs in each trial are not comparable, we do not compare the result of the verifiable CRs trial with the non-verifiable CRs trial. During the analysis plan we therefore did not consider the dependency between the hypotheses behind the two types of trials. The chi-square test will be used to compare individual and sets of CR pass rates between the supported and non supported automatically verifiable CRs, and between the CRs with advice that was framed differently (AP and IN). The binomial test will be used to test whether the number of supported CRs had higher pass rates than the non supported CRs. Statistical analyses will be performed with the R statistical software (R Foundation for Statistical Computing, Vienna, Austria). Standard statistical tests will be used to compare the baseline characteristics of the centers and patients.

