**Design:**

We propose two randomized controlled trials among a group of Dutch GP teams on adherence to ACOVE quality indicators. In both trials a clinical decision support system provides un-intrusive feedback appearing as a color-coded, dynamically updated, list of items needing attention. The first trial pertains to real-time automatically verifiable rules. The second trial concerns non-automatically verifiable rules (adherence cannot be established by the clinical decision support system itself, but the GPs report whether they will adhere to the rules). In both trials we will randomize teams of GPs caring for the same patients into two groups, A and B. For the automatically verifiable rules, group A GPs receive support only for a specific inter-related subset of rules, and group B GPs receive support only for the remainder of the rules. For non-automatically verifiable rules, group A GPs receive feedback framed as actions with positive consequences, and group B GPs receive feedback framed as inaction with negative consequences. GPs indicate whether they adhere to non-automatically verifiable rules. In both trials, the main outcome measure is mean adherence, automatically derived or self-reported, to the rules.

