Finally, although patients usually only see their own GP, the GPs do work in teams. If a patient of one of these GPs requires an immediate appointment, they may see another *paired* GP. To avoid this potential contamination, we will ensure that GPs in a team will be randomized to the same subset. As for the non verifiable CRs, group-A GPs will receive the AP (action-positive) framing, and group-B GPs will receive the IN (inaction-negative) framing. Randomization of GP teams will be concealed; a person who is not responsible for recruiting subjects and has no knowledge of the study conduct will perform it on a computer.

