### Outcome measure

The main outcome measure is the degree of adherence to the automatically verifiable clinical rules (regardless of placement of GPs in teams or centers). Adherence will be calculated in the following ways: 1) as the first primary outcome measure, on which the trial will be powered, we will calculate adherence in terms of the mean pass rate, without distinguishing between specific rules. For this outcome we simply divide the number of times any rule was followed by the number of times any rule was eligible to be followed; 2) we will calculate the pass rates for each rule separately as the second primary outcome measure. The pass rate of a rule is the proportion of times that a rule was followed when it was eligible; and 3) as a secondary outcome we will calculate the number of rules for which there was effect (the pass rate of a rule in its corresponding intervention group was different than in its control group).

We will also calculate the abovementioned measures per patient. Measures pertaining to fall prevention and management will also be investigated separately because fall management comprises a distinct project in itself.

The main outcome measure for the non-verifiable CRs is the degree of adherence as reported by the GPs themselves. In particular, upon receiving advice the GPs can indicate whether they agree (and hence adhere) or disagree (and hence not adhere) with the advice. Adherence will be calculated in the following ways: 1) adherence in terms of the mean pass rate as the first primary outcome measure; 2) adherence for each rule separately, as the second primary outcome; and 3) the number of rules for which there was effect, as a secondary outcome.

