#### Hypothesis about the efficacy of the intervention

A *case* is defined as the situation in which a CR is eligible, meaning that its logical condition is true. Numerous CRs from the same patient can be assessed, and eligibility cases of the same CR are considered to be mutually independent. A power calculation was performed to determine the number of cases needed to detect a minimally clinically relevant effect of the CDSS based on the previously published studies. So far, no studies have been performed that measure the level of adherence to a set of ACOVE QIs in primary care in The Netherlands but Wenger *et al*. [14] showed that a practice-based intervention in the primary-care setting had mean absolute increase pass rates of 21% (from 23 to 44%) and 15% (from 22 to 37%) in two sets of ACOVE CRs.

We assumed 40% adherence in the control group (based on our preliminary baseline analysis) in both verifiable and non verifiable CRs. We can hence make a conservative estimate of an absolute increase of 10% in the mean pass rate of the supported set of CRs in the intervention group compared to the control group. For non-cluster randomization, for a power of 0.80, and two-sided testing at the 0.05 significance level, a total of 408 cases in which CRs are eligible are required in each group.

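### Teams of GPs are randomised, but both primary outcomes in both trials are tested by an unadjusted chi-square test on cases assumed independent, so the nominal 5% level is unsupported; the inflation differs by comparison

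*Protocol article*

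**What the plan says.** **Randomisation.** The abstract (Design) puts it this way: "In both trials we will randomize teams of GPs caring for the same patients into two groups, A and B". Methods agrees. Under Bias control and randomization, the stated safeguard against contamination through shared patients is this: "we will ensure that GPs in a team will be randomized to the same subset".

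**Unit of analysis.** The unit counted is an occasion on which one rule applies to one patient, and one patient may contribute occasions for several rules. Under Hypothesis about the efficacy of the intervention, these are handled as follows: "eligibility cases of the same CR are considered to be mutually independent".

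**Outcomes.** Outcome measure takes adherence to the verifiable rules "regardless of placement of GPs in teams or centers". Its first primary version is one ratio over all rules together, adherent occasions over eligible occasions. Its second takes the rules one at a time: "we will calculate the pass rates for each rule separately as the second primary outcome measure". Both versions recur in the framing trial, based on self-report.

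**Test.** Statistical analyses reads: "The chi-square test will be used to compare individual and sets of CR pass rates between the supported and non supported automatically verifiable CRs". Nothing else is named for either primary outcome, and the framing trial is given the same method. No section mentions an ICC, a design effect, a mixed model, generalised estimating equations or a cluster-level analysis for the adopted design.

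**The concern.** Cases that share a patient, a GP or a team tend to agree with one another. Teams were allocated as a block because their GPs see the same patients, so the design itself recognises the link. A chi-square test that counts every case as a separate piece of information takes its standard error from hundreds of cases, whereas the randomised comparison rests on 15 to 22 teams. The Discussion acknowledges the loss of power from clustering for randomisation by center and by rule, which were rejected, but the adopted design carries no such allowance.

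At stake is a false claim that the decision support system, or one framing style, changes adherence. The planned number of cases is also smaller than a valid analysis may need.

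**Working it through.** **Inputs from the protocol article.** 45 GPs in pairs or triplets; six centers averaging 7,450 patients, about 10% aged 65 or older (The primary care centers GAZO). Control pass rate 40%, increase 10 points, power 0.80, two-sided 0.05, 408 cases per group, non-cluster (Hypothesis section). More than 18 verifiable rules expected (Discussion, At the level of CRs).

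**Derived.** Teams: 45/3 = 15, up to 21 pairs + 1 triplet = 22; I use 20. Patients aged 65+: 6 × 7,450 × 0.10 = 4,470.

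**Assumed.** ICC 0.02 to 0.05; case counts equal across teams; 18 rules sharing cases evenly where stated.

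**Step 1: the plan's figure.** Two proportions, 0.40 against 0.50:
n₀ = [1.96·√(2·0.45·0.55) + 0.8416·√(0.40·0.60 + 0.50·0.50)]² / 0.10² = 387.3, so 388. With continuity correction, n = (n₀/4)·[1 + √(1 + 4/(n₀·0.10))]² = 407.1, so **408**. The plan's figure is reproduced exactly as an independent-cases number and holds no clustering allowance.

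**Step 2: pooled framing comparison.** Each team is wholly in one arm. The design effect is DE = 1 + (m − 1)·ICC, with m cases per team, and the true error of the nominal 5% test is 2·[1 − Φ(1.96/√DE)].

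| Cases per team | ICC | DE | True error |
|---|---|---|---|
| 816/20 = 40.8 | 0.02 | 1.80 | 14% |
| 40.8 | 0.05 | 2.99 | 26% |
| 4,470/20 = 223.5 | 0.02 | 5.45 | 40% |
| 223.5 | 0.05 | 12.1 | 57% |

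The lower rows assume one case per patient aged 65+. Simulation with no true effect agrees within about one percentage point.

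**Step 3: per-rule tests.** These are also parallel comparisons, but m is cases of one rule per team.
- 816/18 = 45 cases per rule, 2.3 per team: DE 1.03 to 1.06, error 5.3% to 5.7% by formula, up to 6.1% by simulation; about 6%.
- 4,470/18 = 248 per rule, 12.4 per team: DE 1.23 to 1.57, error 7.7% to 11.8% by formula; about 8% to 13% over the simulations run.
- Only a rule that applies to nearly every patient aged 65+ reaches the 223-per-team rows of Step 2.

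**Step 4: pooled verifiable comparison.** Each team supplies supported cases (its own subset) and unsupported cases (the other). With equal counts, a constant team effect cancels. With m cases per team per subset, the true variance relative to that assumed by the test is R = (1 − ICC_total) + m·ICC_team×subset, and the error is 2·[1 − Φ(1.96/√R)]. Take ICC_total = 0.05:

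| m | ICC_team×subset | R | True error |
|---|---|---|---|
| 20 or 200 | 0 | 0.95 | 4% |
| 20 | 0.01 | 1.15 | 7% |
| 20 | 0.025 | 1.45 | 10% |
| 200 | 0.01 | 2.95 | 25% to 26% |
| 200 | 0.025 | 5.95 | 42% |

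Unequal counts alone also break the cancellation. In simulation with 18 teams, team ICC 0.05 and no team-by-subset variation, the error is 13% for a 36/10 split per team and 33% for 186/62.

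**Step 5: power in a parallel comparison.** For 18 teams and 816 cases, m = 45.3. At ICC 0.01, DE = 1.44, leaving 408/1.44 = 283 effective cases per arm and power about 0.67. At ICC 0.05, DE = 3.22, leaving 127 and power about 0.36.

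**The case against.** The strongest reply is that the trial is powered on the pooled verifiable pass rate, and that is where the crossed allocation protects most. If teams differ only in general level and cases split evenly, the chi-square test is slightly conservative. This stands. But equal splits and identical team performance across subsets cannot be presumed: rules are grouped by inter-relation (Bias control and randomization) and cover different domains of care (Statistical unit).

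A reader might infer more than the document supports:
- *That false positives far exceed 5% in every primary comparison.* They do not for the pooled verifiable test under the favourable conditions of Step 4, nor for sparse per-rule tests.
- *That the framing figures at 408 per arm apply to each rule.* The 408 is sized for a set of rules, not for one.
- *That confidence intervals are wrong.* None are planned; the point concerns the tests.
- *That repeated record openings count as new cases.* Openings trigger evaluation of the rules, but no section says that each creates a new case.
- *That the outcome definition by itself dictates an unadjusted test.* The parenthesis about teams and centers defines the outcome; the problem comes from the named test and the independence statement.

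The Discussion (At the level of GPs) describes GP-level allocation as the chosen design, against the abstract and Methods. That needs reconciling but does not help, since cases would still cluster within GP.

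Nor can the matter be left to a separate analysis plan or a fuller protocol: the test and the independence assumption are stated here.

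**Conclusion.** The stated analysis does not match the randomisation, and the nominal 5% level is unsupported for both primary outcomes in both trials. The mismatch is certain; its size is conditional on an ICC that the document does not give.

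The framing trial's pooled comparison is the most exposed, and its error is well above 5% even at the low end of the assumed range. Per-rule tests run from barely affected to badly affected, according to how many cases of one rule a team contributes. The pooled verifiable comparison may be sound or strongly anti-conservative, and the chi-square test cannot show which. This should be corrected before analysis. The power in Step 5 is for a parallel comparison; the loss for the pooled verifiable outcome depends on the same team-by-subset variation and case split.

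**What to change.** 1. In Statistical analyses, replace the chi-square test with methods that respect team randomisation.
   - *Pooled comparisons:* a mixed logistic model with rule fixed effects, a support (or framing) effect, and random effects for team, team-by-subset (verifiable trial) and patient, with a small-sample correction for 15 to 22 teams. A team-level permutation test that re-randomises teams is an alternative.
   - *Per-rule comparisons:* the team-level permutation test. With two or three cases of a rule per team, a mixed model may not be estimable.
2. Delete the independence statement under Hypothesis about the efficacy of the intervention.
3. Restate the 408 cases per group and 0.80 power with a justified ICC, separately for the pooled verifiable and the framing comparison. Extra cases from the same teams raise m and hence DE, so multiplying 408 by a fixed DE is not enough.

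The cost is revised wording, a little more programming, wider but honest uncertainty and a less favourable stated power. No new data have to be collected.

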#### Bias control and randomization

Randomization will take place after measurement of baseline data. Every CR will be randomized into two groups of GP teams. Recall that while a patient will usually be seen by only one GP, a GP team consists of two or three GPs sharing care for the same sub-population of patients. When a patient’s official GP is absent, another GP from the team may see the patient.

Based on the baseline measurement and the expected room for improvement, randomization at the GP level is the most appropriate choice in terms of power and also practicality. However, this randomization choice will be adapted in order to control for possible contamination and biases. The discussion below pertains to verifiable CRs because they are the most prone to contamination.

We assume that contamination between GPs, especially in the same center, is relatively high when some GPs receive support for a rule (intervention) and the others none (control). To reduce the probability of this kind of contamination we have two groups of GPs, A and B. Every GP in group A will receive support for a specific subset of supported CRs (subset A) and no support for the rest of the CRs (subset B). By the same token, Every GP in group B will receive support for subset B and no support for subset A. This means that for about half the CRs (subset A) the GPs in group A form the intervention group and the GPs in group B form the control group, and vice versa for the CRs in subset B. All GPs will hence receive some kind of support, which means they do not have to feel that they are in the control group. A disadvantage of this approach is that some CRs are inter-related and improvement in one can explicitly or implicitly lead to improvement in the related one, even if it is not supported. For example, if one CR is supported by giving a reminder to order a laboratory test, and the same laboratory test is required by another CR that is not supported, ordering the laboratory test will be registered as adherence to both CRs. Therefore we will group all inter-related subsets of CRs in either subset A or subset B, elements of the inter-related subsets will hence never appear in both groups.

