### At the level of CRs

In this type of design every CR is randomly assigned to GPs for decision support: some of the GPs will be in the intervention/AP group of the CR (receiving feedback or AP framing about it) and the other GPs will be in the control/IN group for that CR. This means that every GP will be in the intervention/AP group for a randomly selected subset of CRs and in the control/IN group for the complementary set of CRs. It is very probable that every GP will have a unique set of CRs for support and framing, different to any other GP. The advantage is that there are more CRs (expected to be more than 18 verifiable CRs) to be randomly allocated than centers, yielding higher power and hence a shorter minimum follow-up period required to detect an effect. The disadvantage is that contamination between GPs is still possible. However, an additional problem is that the CRs can be inter-related (for example because they pertain to the same condition, such as falls), which leads to contamination, because support for one CR may not only influence the GPʼs behavior for that CR but also for other, related CRs, even if they are not supported. The CRs must therefore be grouped together and all CRs in each group should either be supported or not. In effect, we then have a cluster-randomized trial in which the cluster consists of the CR groups. Hence the power disadvantages apply again due to the low number of resulting clusters (groups of CRs) and the possible need to stratify randomization to have similar GP and patient characteristics for each cluster.

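### The secondary rule count is defined without a direction but tested with one, and its binomial test assumes independent rules, so the p-value is not guaranteed to be calibrated

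*Protocol article*

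**What the plan says.** All references are to the protocol article.

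- **Definition.** *Outcome measure* makes the number of rules with an effect a secondary outcome of the verifiable-rules trial. An effect means that "the pass rate of a rule in its corresponding intervention group was different than in its control group". No direction or threshold is given.
- **Test.** *Statistical analyses* says: "The binomial test will be used to test whether the number of supported CRs had higher pass rates than the non supported CRs". It states neither sidedness nor a null proportion. The sample-size section uses two-sided testing at 5%, for the mean pass rate.
- **Dependence between rules.** *Bias control and randomization* says that "some CRs are inter-related and improvement in one can explicitly or implicitly lead to improvement in the related one", and gives the example of one laboratory order that registers as adherence to two rules. The response is one of design: "we will group all inter-related subsets of CRs in either subset A or subset B".
- **Shared units.** GP teams are randomised whole, so the same teams supply every rule, and several rules can be assessed on one patient. The only independence assumption stated is that "eligibility cases of the same CR are considered to be mutually independent". Nothing is said about independence between rules.

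**The concern.** There are two separate faults.

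**Outcome and test do not match.** A count of rules that are *different* includes rules that got worse. A test of *higher* uses another count with another null. A result such as X of Y rules improved is easily quoted, and a reader could not tell from these two sentences which count is meant or what the p-value refers to.

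**The rules are not independent trials.** The binomial test treats each rule as a separate coin toss. If related rules rise or fall together by chance, there are fewer effective tosses than rules and the test rejects too often. A chance difference between the two groups of teams acts the other way. It raises the supported-minus-unsupported difference in one subset and lowers it in the other, so the signs cancel and the test rejects too rarely. In either case the nominal p-value does not describe the design that was run.

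**Working it through.** **The plan's own figure.** The only sample-size figure is 408 cases per group for the mean pass rate, 40% against 50%, two-sided 5%, power 0.80.

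- Without continuity correction: n = [1.960·√(2·0.45·0.55) + 0.842·√(0.40·0.60 + 0.50·0.50)]² / 0.10² = 387.3, so 388.
- With continuity correction: (387.3/4)·[1 + √(1 + 4/(387.3·0.10))]² = 407.1, so 408.

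The figure reproduces and does not involve the rule count. The article gives no figure for the rule-count test.

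**Inputs for the rule-count test.** The number of rules is taken as 18, because *At the level of CRs* expects more than 18. The null probability of 0.5 that a rule is higher under support is the usual reading of such a test; the article does not state it. Group sizes and correlations are assumptions, since the article gives neither.

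**Step 1: the wording matters.** Let X be the number of rules higher under support, X ~ Bin(18, 0.5).

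- P(X ≥ 14) = 4,048/262,144 = 0.0154. Two-sided, 14 of 18 are needed and the size is 0.031.
- P(X ≥ 13) = 12,616/262,144 = 0.048. So 13 of 18 gives p = 0.048 one-sided and 0.096 two-sided.
- If *different* means significant at 5% in either direction, the null proportion is 0.05. Then P(≥ 3 of 18) = 0.058 and P(≥ 4 of 18) = 0.011. This is a different test with a different threshold.

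**Step 2: size when rules are dependent.** Each rule's difference is simulated as a standard normal value under the null, with correlation ρ inside equal groups of related rules. The two-sided test rejects at 14 or more, or 4 or fewer, of 18 (200,000 to 400,000 runs per row).

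| Assumed structure | Two-sided size |
|---|---|
| Independent rules | 3.1% |
| Pairs, ρ = 0.1 / 0.3 / 0.5 | 3.6% / 4.9% / 6.4% |
| Triplets, ρ = 0.1 / 0.3 / 0.5 | 4.3% / 6.9% / 9.9% |
| Opposing A/B team effect only, ρ = 0.3 / 0.5 | 1.8% / 1.4% |

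**Step 3: both mechanisms together (six groups of three).**

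| Group component | Team component | Two-sided size |
|---|---|---|
| 0.2 | 0.1 | 5.0% |
| 0.1 | 0.2 | 3.3% |
| 0.3 | 0.1 | 6.4% |
| 0.5 | 0.3 | 9.5% |

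In the first two rows the components sum to a within-group correlation of 0.3. The size then depends on how much of that correlation comes from related rules and how much from teams.

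**The case against.** The case on the other side is substantial, and several parts of it stand.

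- **Harm is not hidden.** A reader might infer that the trial cannot tell benefit from harm. It can. The pass rate of each rule is the second primary outcome and is compared by chi-square, so a rule that worsened is visible there. The fault lies in the summary count only.
- **The literal reading may be uncharitable.** An effect could mean a significant chi-square result for that rule, and detail on sidedness may sit in a fuller plan. That explains *different*, but it does not reconcile it with *higher*: the two sentences still describe different counts.
- **Much of the cited dependence concerns spillover of support.** *Bias control and randomization* speaks of improvement in one rule carrying over to another. That is dependence when the intervention works, and by itself it does not raise the false-positive rate. The remark that "the power disadvantages apply again due to the low number of resulting clusters (groups of CRs" belongs to a randomisation option that was not chosen. What remains as a source of correlation under the null is the shared laboratory order and the shared patients and teams. That is enough to break the independence assumption, though not to say by how much.
- **Inflation is possible, not shown.** At weak correlation the two-sided size stays below 5%, and the two mechanisms partly offset. A reader might conclude that the test is plainly anti-conservative; the article does not support that.
- **The framing trial.** It has the same kind of outcome, "the number of rules for which there was effect, as a secondary outcome", and one might extend the criticism to it. *Statistical analyses* words the binomial test only for supported against non-supported rules, so no error rate is claimed for framing.

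**Conclusion.** The point holds for a secondary outcome. The definition and the test of the rule count disagree on direction, and the test rests on independence between rules that the protocol's own description contradicts. The p-value is therefore not guaranteed to be calibrated. For 18 rules and a nominal two-sided size of 3.1%, the true size under the assumed structures lies between about 1.4% and 10%, and its direction relative to nominal is unknown. The range rests on assumed group sizes and correlations, on a null probability of 0.5, and on taking 18 for a number expected to be larger. The mean pass rate comparison and the 408 cases are not affected by this point.

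**What to change.** In *Outcome measure* and *Statistical analyses*, use one definition: the number of rules whose pass rate is higher in the supported than in the unsupported group, with the number lower reported beside it. State that the test is two-sided. Replace the binomial p-value by a permutation p-value: re-randomise the GP teams to A and B as in the actual allocation, keep the rule subsets fixed, recount, and locate the observed count in that distribution. This respects the unit that was randomised and keeps the dependence between rules. Reporting the count descriptively, without a p-value, is an adequate alternative.

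A sign test on groups of related rules is a weak substitute: with six groups all six must agree (two-sided p = 2·0.5⁶ = 0.031).

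The cost is two revised sentences and a short program, with no new data. The permutation p-value may be less favourable than the binomial one.
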